### Randomization and Allocation Concealment

Random numbers will be generated by a computerized random number table generator through the stratified block randomization method of the SAS package (Version 9.4; SAS institute Inc., Cary, NC, USA) with a random block size. The random number table will be prepared by an independent, blinded statistician. Two block numbers will be randomly used to prevent allocation guessing by researchers. A stratified random number table will be generated according to the severity of chronic neck pain (PI-NRS score range from the 4 to 6 group vs the 7 to 10 group). The random number table file will be protected by a password, and the independent, blinded statistician, who is not involved in the recruitment, acupuncture treatment or assessment, will manage the table. A random allocation will be conducted at visit 1 to participants who provide informed consent. When a participant meets the inclusion criteria, the two types of treatment will be explained to him or her. Acupuncture will be explained as “classical acupuncture, typically used in Korean medicine clinics” and sham acupuncture as “non-classical acupuncture, rarely used in Korean medicine clinics” [14]. To ensure allocation concealment, the participants will be randomized according to the random number table by the independent researcher, and the allocated group information will be sent by an e-mail. The e-mail will be printed out and stored as a source document.

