### Sample size calculation

The primary outcome of our study is overall neck pain, which is measured by the PI-NRS change from baseline to 4 weeks. In chronic neck pain, the minimum clinically important difference (MCID) is a 1.5 unit change in the PI-NRS score [25]. According to a previous study [40], we assumed that the SD of PI-NRS change from baseline to 4 weeks will be 1.88 in the treatment group and 2.21 in the control group, each with a population correlation between the baseline and follow-up scores that was estimated as 0.5. In a superiority test, we assumed that the PI-NRS difference between the two groups will be 1.5, which is identical to the MCID. With a 5 % of significance level (α = 0.05, 2-sided) and 80 % power (1-ß = 0.8), the sample size was calculated as 31 participants in each group using G*Power 3.13 software (Franz Faul, Universität Kiel, Germany). Considering a 15 % drop-out rate, a total of 74 participants is needed.

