### Statistical analysis

The analysis set will consist of a full analysis set (FAS), per protocol (PP) set and safety set. The safety set will include any participants who were randomly assigned and received at least one acupuncture treatment. The FAS will include data indicating that the treatment was as close to intention to treat (ITT) as possible. In addition to the criteria of the safety set, to be included in the FAS participants have to be evaluated for the primary outcome at least once. To be included in the PP set, participants have to receive more than 6 sessions (75 %) of treatment. The FAS will be used in the main analysis. The primary outcome of our research is the difference in PI-NRS score change from the baseline to week 4 between the two groups. Sensitivity analysis will be performed by comparing the results from PP analysis and ITT analysis, and the last observation carried forward (LOCF) method will be used to handle the missing data.

For the descriptive analysis, data will be evaluated for normality and log-transformed when necessary. A two student’s t-test or a Wilcoxon rank sum test for continuous data and a chi-squared test or Fisher’s exact test for categorical data will be performed according to whether the data are normally distributed or skewed.

For a confirmatory analysis, primary efficacy endpoint, the change from baseline to week 4 in PI-NRS, will be evaluated using student’s t-test or Wilcoxon rank sum test. This result will be compared with adjusted result using an analysis of covariance (ANCOVA) with the baseline measurement of PI-NRS as a covariate, the treatment group as a fixed effect. The secondary efficacy endpoint will be evaluated using a student’s t-test or Wilcoxon rank sum test for continuous data or chi-squared test or Fisher’s exact test for categorical data. All of the statistical analyses will be performed SAS package (Version 9.4; SAS institute Inc., Cary, NC, USA) by a statistician blinded to patient allocation, and a significance level of 5 % will be used.

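### The confirmatory PI-NRS test is an unadjusted t-test or Wilcoxon test picked on the data; making the already planned baseline-adjusted ANCOVA the single primary analysis is a free gain

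*Protocol article*

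**What the plan says.** The Statistical analysis section of the protocol article defines the target of the trial: "The primary outcome of our research is the difference in PI-NRS score change from the baseline to week 4 between the two groups". The paragraph on the confirmatory analysis names, for this endpoint, a Student's "t-test or Wilcoxon rank sum test. This result will be compared with adjusted result using an analysis of covariance (ANCOVA"), and specifies the ANCOVA "with the baseline measurement of PI-NRS as a covariate, the treatment group as a fixed effect".

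The confirmatory paragraph does not say when the t-test applies and when the Wilcoxon test does. The only rule is in the preceding paragraph, on descriptive analysis, where tests "will be performed according to whether the data are normally distributed or skewed". No test of normality and no cut-off is given there. Continuous secondary endpoints are also to be analysed by t-test or Wilcoxon test, without baseline adjustment.

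Two other sections bear on this. Under Randomization and Allocation Concealment: "A stratified random number table will be generated according to the severity of chronic neck pain", with bands PI-NRS 4 to 6 and 7 to 10. Under Sample size calculation, the SD of change is 1.88 and 2.21 in the two arms, with "a population correlation between the baseline and follow-up scores that was estimated as 0.5", and a difference of 1.5 points is assumed.

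**The concern.** Baseline PI-NRS is measured in every participant, defines the randomisation strata, and is expected to correlate 0.5 with the week-4 score. The test that decides the trial does not use it. A change score subtracts the baseline with a coefficient fixed at one, whereas ANCOVA estimates the coefficient. At a given correlation and ratio of SDs, the ANCOVA residual variance is therefore never larger than the change-score variance. The price is one degree of freedom.

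The form of the test also depends on how the outcome data look. The t-test addresses a difference in means, which is what the sample size is built on. The Wilcoxon test is a rank comparison and does not test or estimate a 1.5-point mean difference.

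Finally, the text does not say what follows if the unadjusted result and the ANCOVA fall on opposite sides of 5 %. At stake are some precision and a primary analysis that is fully fixed before the data are seen.

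**Working it through.** **Inputs from the Sample size calculation section.** Difference 1.5; SD of change 1.88 and 2.21; correlation 0.5; two-sided 5 %; power 80 %; 31 per arm; 15 % drop-out; 74 in total.

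**Step 1: the plan's own figure.** Averaged SD of change = √((1.88² + 2.21²)/2) = √4.209 = 2.052. Standardised difference = 1.5/2.052 = 0.731. The two-sample t-test (noncentral t) gives power 79.5 % at 30 per arm and 80.8 % at 31. Drop-out: 31/0.85 = 36.5, so 37 per arm and 74 in total. The stated size reproduces, and it is a size for the unadjusted t-test.

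**Step 2: if Wilcoxon replaces the t-test.** On normal data its asymptotic relative efficiency is 3/π = 0.955. Power at 31 per arm becomes about 79 %, and about 32 per arm would be needed. The power loss is small; the change of target is the larger point.

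**Step 3: what ANCOVA would save.** Write B for the baseline SD, F for the week-4 SD, ρ = 0.5 and C = 2.052 for the SD of change.

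- C² = B² + F² − 2ρBF, so F = ρB + √(C² − (1 − ρ²)B²).
- ANCOVA residual variance = (1 − ρ²)F² = 0.75F².
- Saving = 1 − 0.75F²/C².

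The article gives no baseline SD, so B is an assumption, shown over a range:

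| Assumed baseline SD | Implied week-4 SD | Residual SD | Variance saved | ANCOVA power, 31 per arm |
|---|---|---|---|---|
| 1.3 | 2.37 | 2.05 | 0.3 % | 81.0 % |
| 1.5 | 2.34 | 2.02 | 2.6 % | 81.8 % |
| 1.7 | 2.28 | 1.97 | 7.5 % | 83.7 % |
| 2.0 | 2.10 | 1.82 | 21.4 % | 89.1 % |
| 2.05 (equal to week 4) | 2.05 | 1.78 | 25 % | 90.5 % |

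The unadjusted t-test stays at 80.8 % in every row.

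**Step 4: which rows are plausible.** The strata admit scores 4 to 10. A flat distribution over those seven integers has variance (7² − 1)/12 = 4, so SD 2.0. The 25 % row needs a baseline more spread out than flat over the eligible range. It is close to a best case.

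**Step 5: type I error, by simulation under no effect at 31 per arm.** With normal data and equal SDs (20,000 runs), the rejection rates were t-test 4.9 %, Wilcoxon 4.8 %, ANCOVA 4.7 %, and t-test or Wilcoxon chosen by a normality pretest 5.0 %. Claiming success if either the pretest-chosen test or ANCOVA is below 5 % gave 7.2 %. With integer scores, baseline kept within 4 to 10 and a baseline-to-week-4 SD ratio of 0.64 to 1.0, that figure was 5.8 to 7.0 %. With the true difference at 1.5 in the same setting, the two results fell on opposite sides of 5 % in about 5 to 11 % of trials.

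**The case against.** The strongest reply is that nothing here is an error. A change-score t-test is valid in a randomised trial, the trial is sized for exactly that test, and the planned power is met. The unadjusted test stands in the paragraph on the confirmatory analysis, so ANCOVA reads naturally as supportive. The statistician is blinded to allocation and the blind holds until data lock, which limits choosing a test in a known favourable direction. A normality criterion may sit in a fuller document that is not shown. All of this stands, and it limits the point to a better choice of method.

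Three stronger readings are tempting, and the document does not support them:

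- *The plan wastes a quarter of the variance.* A reader might infer this from the correlation of 0.5. It holds only if the baseline SD is as large as the week-4 SD. The article does not say so, and entry restricted to scores of 4 and above works against it.
- *Three p-values compete with no rule to decide.* The t-test and Wilcoxon test are alternatives, so there are two primary results. One of them is labelled confirmatory, and a loose rule for choosing its form is given.
- *The type I error is about 7 %.* That rate belongs to claiming the more favourable result, which the article does not plan. A normality pretest alone gave 5.0 % on normal data.

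What the reply does not meet is the choice that the article does make: the less efficient analysis decides, its form depends on the outcome data, and the better one is already planned alongside it.

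**Conclusion.** The point holds as a free improvement. The article fixes an unadjusted, data-dependent t-test or Wilcoxon test as confirmatory and leaves ANCOVA on the stratifying baseline score as a comparison. The unadjusted t-test is valid and delivers 80.8 % power at 31 per arm, so no planned power is lost.

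The gain from promoting ANCOVA is between almost nothing and 25 % of the residual variance, or power of 81 % to 90.5 % at 31 per arm. This rests on the plan's SD of change and correlation, and on assumed baseline SDs of 1.3 to 2.05. The upper end is unlikely given the entry range.

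Naming one analysis also keeps the test aligned with the 1.5-point mean difference, and it closes off a choice between results that would carry a type I error of about 6 to 7 % if it were made.

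**What to change.** In the Statistical analysis section, name one primary analysis: ANCOVA of week-4 PI-NRS (or of change, which gives the same treatment estimate) on treatment and continuous baseline PI-NRS, tested at two-sided 5 %, reporting the adjusted mean difference with its 95 % CI. State that the t-test and Wilcoxon test are supportive and do not alter the primary conclusion. Use the same baseline-adjusted model for continuous secondary outcomes that have a baseline value: NDI, CROM, HRV, PSS, EQ-5D, pressure pain threshold and biomarkers.

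The cost is wording and one degree of freedom. The planned ANCOVA already has this covariate, Table 1 already schedules baseline PI-NRS, and the sample size can stay at 74.

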#### Secondary endpoint

The secondary outcomes include a change from the baseline of clinical relevance for pain (ratio of change greater than 1.5 in PI-NRS and decrease greater than 30 % and 50 % on the PI-NRS), function (NDI and Cervical Range of Motion (CROM)), autonomic and psychometric measurements (Heart Rate Variability (HRV) and Perceived Stress Scale (PSS)), quality of life (EuroQol (EQ-5D)), global assessment (Patient Global Impression of Change (PGIC)), semi-objective outcomes (pressure pain threshold (PPT), consumption of rescue medicine, days of restricted activity), immunologic and stress markers and adverse events.

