##### Global assessment

The participants’ global assessment will be performed using the PGIC, a self-reported 7-point categorical scale used to evaluate the overall improvement after treatment [24]. Participants will be asked to evaluate themselves subjectively regarding the improvement of their symptoms at the 4th week compared to baseline by selecting one of the following seven options: 1) very much improved, 2) much improved, 3) minimally improved, 4) no change, 5) minimally worse, 6) much worse or 7) very much worse.

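### The PGIC is an ordered seven-level scale labelled categorical, and the only tests given for categorical secondary endpoints ignore order; the plan should name an ordinal test for it

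*Protocol article*

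**What the plan says.** All references are to the protocol article.

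- **Global assessment** calls the PGIC "a self-reported 7-point categorical scale used to evaluate the overall improvement after treatment". The options are "1) very much improved, 2) much improved, 3) minimally improved, 4) no change, 5) minimally worse, 6) much worse or 7) very much worse". The patient gives the rating in week 4, looking back to baseline.
- **Secondary endpoint** includes "global assessment (Patient Global Impression of Change (PGIC" in a list introduced as change from baseline. The abstract does the same, under mean change from baseline.
- **Table 1** schedules the PGIC at visit 8 only.
- **Statistical analysis** chooses the test for secondary endpoints by data type: Student's t-test or "Wilcoxon rank sum test for continuous data or chi-squared test" or Fisher's exact test, the last two being for categorical data. It does not mention ordinal data or the PGIC.
- **Pain** (under the secondary endpoints) defines responder cut-offs for the PI-NRS at 1.5 points, 30 % and 50 %. No such cut-off is given for the PGIC.

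**The concern.** The seven PGIC levels have a natural order. A chi-squared or Fisher test on the 2 x 7 table takes no account of it: shuffling the columns would leave the p-value unchanged. Such a test spreads its sensitivity over every possible difference in shape between the arms (6 degrees of freedom), whereas the question is whether one arm shifts towards improvement (1 degree of freedom). With about 31 to 37 patients per arm, the levels at the worse end may also be nearly empty.

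A real shift in the patients' own global rating could therefore be missed. A significant result would establish only that the distributions differ; the direction would have to be read from the percentages. This matters because the article sets out to judge clinical relevance as well as statistical significance, and the PGIC is its only global assessment.

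The change-from-baseline wording adds a smaller inconsistency. With no baseline PGIC value, no change score can be computed; the rating is itself a judgement of change.

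**Working it through.** **1. The plan's own figure.** Inputs from Sample size calculation: "we assumed that the PI-NRS difference between the two groups will be 1.5"; the SD of change "will be 1.88 in the treatment group and 2.21 in the control group"; "significance level (α = 0.05, 2-sided"); 80 % power; 15 % drop-out.

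- Pooled SD = √((1.88² + 2.21²)/2) = 2.052.
- Standardised effect d = 1.5/2.052 = 0.731.
- Two-sample t-test (noncentral t): power is 79.5 % with 30 per arm and 80.8 % with 31, so 31 per arm.
- 31/0.85 = 36.5, so 37 per arm and 74 in total.

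The stated sample size is reproduced. It applies to the primary endpoint; no power is stated for the PGIC.

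**2. Large-sample comparison.** A 1-df test at two-sided 5 % has 80 % power when its noncentrality is 7.85. Keep that noncentrality and raise the degrees of freedom:

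| Levels in use | df | 5 % critical value | Power |
|---|---|---|---|
| ordinal test | 1 | 3.84 | 80 % |
| 4 | 3 | 7.81 | 64 % |
| 5 | 4 | 9.49 | 60 % |
| 7 | 6 | 12.59 | 52 % |

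With all seven levels in use the fall is 28 points, or 28/80 = 35 % in relative terms. With four or five levels it is 16 to 20 points, or 20 to 25 %.

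**3. Simulation at the trial's size.** Assumptions, none of them from the documents: a latent normal shift of 0.731 SD towards improvement, applied to four control-arm distributions (percentages from very much improved to very much worse):

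- A: 3, 15, 35, 35, 8, 3, 1
- B: 10, 15, 20, 25, 15, 10, 5
- C: equal across the seven levels
- D: 1, 9, 40, 45, 4, 1, 0

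There were 2,000 simulated trials per setting. Pearson chi-squared was computed on the non-empty columns, Fisher's test by Monte Carlo, and Wilcoxon with tie correction. Relative loss = 1 − (power of unordered test)/(power of Wilcoxon).

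| Control | n per arm | Chi-squared | Fisher | Wilcoxon | Loss, chi-squared | Loss, Fisher |
|---|---|---|---|---|---|---|
| A | 31 | 42.7 % | 49.0 % | 76.3 % | 44 % | 36 % |
| A | 37 | 54.3 % | 60.6 % | 84.8 % | 36 % | 28 % |
| B | 31 | 40.2 % | 43.8 % | 77.2 % | 48 % | 43 % |
| B | 37 | 52.9 % | 56.7 % | 83.7 % | 37 % | 32 % |
| C | 31 | 44.7 % | 46.5 % | 76.3 % | 41 % | 39 % |
| C | 37 | 52.2 % | 54.1 % | 81.9 % | 36 % | 34 % |
| D | 31 | 41.7 % | 49.0 % | 73.4 % | 43 % | 33 % |
| D | 37 | 53.6 % | 62.1 % | 82.0 % | 35 % | 24 % |

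A separate run of setting D at 37 per arm gave 53.3 % against 80.9 %, a loss of 34 %, which sets the lower end for chi-squared. In absolute terms the loss runs from 82.0 − 62.1 = 20 points (Fisher, D, 37 per arm) to 77.2 − 40.2 = 37 points (chi-squared, B, 31 per arm).

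**4. Sensitivity to the assumed effect.** Across other shifts the relative loss for chi-squared runs from about 20 % for large effects to about 60 % for small ones. For example, under control C at 37 per arm, a 0.5 SD shift gives 25.4 % against 52.0 % (loss 51 %), and a 0.9 SD shift gives 75.1 % against 95.2 % (loss 21 %).

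**5. Sparse tables.** With no true difference and rare end levels (A and D), chi-squared rejected in about 2 to 3 % of trials instead of 5 %. This is why Fisher loses somewhat less.

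**The case against.** The strongest reply is that the plan never assigns a test to the PGIC. Statistical analysis states a general rule, and the link rests on one word in the description of the instrument. The categorical branch has obvious users without it, namely the PI-NRS responder proportions. The change-from-baseline wording, taken literally, points to the continuous branch, where Wilcoxon already applies. On this view the test is merely unstated, and an unseen analysis plan would supply it.

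Part of this stands. A reader might infer that the plan explicitly prescribes a chi-squared test for the PGIC; it does not, and the assignment follows only from reading two sections together. But categorical is the only explicit data type given for the PGIC, the Wilcoxon test is reserved for continuous data, and a change from baseline cannot be computed from a single rating. An analysis plan that followed the stated rule would carry the problem forward. The point concerns a stated rule that fits badly, not an omitted detail.

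A reader might also infer that a fixed share of power, such as a third, is lost. The documents do not support one number: they give neither a PGIC effect nor a distribution, percentage points and relative loss must be kept apart, and Fisher, the likely choice for sparse tables, loses less than chi-squared.

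Two further replies have some force. Percentages per arm would show direction even after an unordered test. And a binary cut of the PGIC would make chi-squared or Fisher suitable, but none is specified. In simulation, a cut at much improved or better still gave only about 48 to 69 % power, against 73 to 85 % for Wilcoxon.

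**Conclusion.** The point holds as a minor one that is free to correct. On its plainest reading the stated rule gives the PGIC an order-blind 2 x 7 test, although a suitable test is already in the plan.

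The size depends on a shift borrowed from the primary endpoint and on invented PGIC distributions, so it should be quoted only as the range in the working, with those assumptions attached. The direction of the loss was the same in every setting with a true shift.

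It would be wrong to infer a threat to the trial's main conclusion. The PGIC is one secondary outcome among many, no power is claimed for it, and the primary PI-NRS analysis and the sample size are untouched. The change-from-baseline listing is a matter of wording.

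**What to change.** Add one sentence to Statistical analysis: the week-4 PGIC is treated as ordinal and compared between arms with the Wilcoxon rank-sum test. Optionally, report a common odds ratio with 95 % CI from a proportional-odds model, which also gives direction and size. Keep chi-squared and Fisher for the binary PI-NRS responder outcomes. Take the PGIC out of the change-from-baseline lists in the abstract and under Secondary endpoint, and describe it as a week-4 rating. If a PGIC responder proportion is wanted as well, fix its cut-off before unblinding.

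The cost is a few words. Data collection, visits and sample size do not change.

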### Design and setting

This study is an equal randomized, stratified (11-point pain intensity numerical rating scale (PI-NRS) score ranging from 4 to 6 in one group and 7 to 10 in one group), patient- and assessor-blinded, sham controlled, parallel-group, single center, clinical trial conducted in Korea.

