#### Study plan

After oral and written consent is obtained from each patient, subject information will be collected at the first visit. After a participant voluntarily consents to the study, they will be screened using inclusion/exclusion criteria at the first visit. If the participants take the pain medications, a ten-day wash-out period will be needed. At the end of the screening phase, if an eligible participant meets the study criteria with moderate (PI-NRS score range from 4 to 6) or severe (PI-NRS score range from 7 to 10) chronic neck pain, then the subject will be randomly allocated into 1 of 2 groups (the MMRA or sham acupuncture group) with a 1:1 allocation ratio. The MMRA group and sham acupuncture group will receive a total of 8 acupuncture treatment sessions during 4 weeks. MMRA acupuncture will be conducted at traditional acupuncture points, or ashi points, with deqi sensation. Sham acupuncture will be performed at non-acupuncture points without deqi sensation using a PSD. After a 4-week treatment, primary outcome measurements will be evaluated.

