##### Pain

The mean change of pain intensity from baseline at 1, 2, 3 weeks will be measured by the PI-NRS. Clinical relevance will be assessed using the ratio of participants in each group who reported PI-NRS scores that reduced greater than 1.5 points or 30 % and 50 % at 4 weeks from the baseline PI-NRS scores. We pre-defined the type of improvements as follows: a PI-NRS reduction of 1.5 points as minimally important; 30 % reduction from baseline as moderately important; and 50 % reduction as substantially important [26]. Therefore, in this trial, both the absolute and relative score change will be used to analyze the clinical relevance.

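### Randomisation is stratified by baseline pain severity, but the three secondary PI-NRS responder outcomes get an unstratified chi-squared or Fisher test: valid, at most mildly conservative, and free to improve

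*Protocol article*

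**What the plan says.** All references are to the protocol article.

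- **Design and setting:** "This study is an equal randomized, stratified (11-point pain intensity numerical rating scale (PI-NRS) score ranging from 4 to 6" in one stratum and 7 to 10 in the other.
- **Randomization and Allocation Concealment:** "A stratified random number table will be generated according to the severity of chronic neck pain". Study plan adds that patients are allocated "with a 1:1 allocation ratio".
- **Secondary endpoint, Pain:** "Clinical relevance will be assessed using the ratio of participants in each group who reported PI-NRS scores that reduced greater than 1.5 points", or by 30 % and 50 %, at 4 weeks. The three cut-offs are labelled minimally, moderately and substantially important. None is ranked above the others.
- **Statistical analysis:** secondary endpoints are compared by t-test or Wilcoxon test "for continuous data or chi-squared test or Fisher’s exact test for categorical data". No stratum term appears. The only baseline adjustment is an ANCOVA on baseline PI-NRS, set beside the unadjusted test of the primary change score.

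**The concern.** The stratification factor is the baseline value of the scale on which response is defined. An absolute fall of more than 1.5 points may be easier to reach from 7-10 than from 4-6. If so, the stratum predicts response. The design then removes between-stratum variation from the treatment comparison, while the planned test leaves it in the standard error. The test would run below its nominal level and give up some of the precision that stratification bought.

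The Background section faults earlier trials for neglecting the MCID and says that it will guide interpretation here. The responder proportions are where this is done, so an inefficient test of them has some cost.

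**Working it through.** **1. The plan's own figure.** Inputs from Sample size calculation: SD of change 1.88 and 2.21, "α = 0.05, 2-sided", 80 % power, and "we assumed that the PI-NRS difference between the two groups will be 1.5". Pooled SD = √[(1.88² + 2.21²)/2] = √4.209 = 2.05. The noncentral t gives 79.5 % power at 30 per arm and 80.8 % at 31, which agrees with "the sample size was calculated as 31 participants in each group". Dropout: 31/0.85 = 36.5, so 37 per arm and 74 in total. This sizing covers the primary change score only.

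**2. What ignoring the stratum does.** Let a share w of patients be in the severe stratum, with response rates p₂ (severe) and p₁ (moderate) and overall rate p. With arms balanced within strata, the true variance of the treatment contrast is proportional to p(1−p) − w(1−w)(p₂−p₁)². The unstratified test uses p(1−p). With R the ratio of true to assumed variance, the actual level is about 2[1 − Φ(1.96/√R)], which cannot exceed 5 % in this approximation.

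Two assumed cases, w = 0.4 and p₁ = 0.30:
- p₂ = 0.462 (odds ratio 2): p = 0.365, R = 1 − 0.24 × 0.162²/0.232 = 0.973, level about 4.7 %.
- p₂ = 0.682 (odds ratio 5): p = 0.453, R = 1 − 0.24 × 0.382²/0.248 = 0.859, level about 3.4 %.

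So the question is how strongly the stratum predicts response.

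**3. What the plan implies.** Sample size calculation gives a baseline/follow-up correlation of 0.5 but no baseline SD. With baseline SD B and SD of change C = 2.05, the follow-up SD is F = [B + √(4C² − 3B²)]/2, and the correlation of baseline with reduction is (B − 0.5F)/C:
- B = 1.5: F = 2.34, correlation 0.16
- B = 1.7: F = 2.28, correlation 0.27
- B = 2.05: F = 2.05, correlation 0.50

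Entry limits baseline to 4-10. Even a uniform spread over those seven integers has SD √[(7² − 1)/12] = 2.0. A correlation of 0.5 therefore needs a baseline spread slightly wider than uniform. Assumed unimodal distributions with SD 1.46-1.60 give 0.14-0.22.

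**4. Simulation of the 1.5-point rule.** The plan's SDs and 1.5-point effect were used, with integer baselines 4-10 and arms balanced within strata. The mean sham improvement of 1.0 and the baseline distributions are assumptions. CMH is the Cochran-Mantel-Haenszel test by stratum.

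| Baseline-change correlation | N | Chi-squared level | CMH level | Power gain from CMH (points) |
|---|---|---|---|---|
| 0.14-0.22 | 62 | 5.0-5.2 % | 5.1-5.2 % | 0.1-0.2 |
| 0.14-0.22 | 74 | 4.3-4.6 % | 4.7 % | 0.1-0.6 |
| 0.3 | 62 and 74 | 4.2-4.7 % | 4.7-5.1 % | 0.5-1.4 |
| 0.5 | 62 and 74 | 3.2-4.0 % | 4.6-5.2 % | 2-4 |

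The stratum odds ratio is about 2.4-2.7 at correlation 0.3 and 4.8-5.6 at 0.5. In a separate grid that fixed the stratum response rates directly (N = 74), the gain was at most 0.9 points up to odds ratio 2, 1.2-2.3 at 3 and 2.7-5.4 at 5.

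**5. The 30 % and 50 % rules.** On integer scores a fall of more than 1.5 means 2 points from any baseline. A 30 % fall means 2 points from 4, 5 or 6 (1.2, 1.5, 1.8) but 3 points from 7, 8 or 9 (2.1, 2.4, 2.7). The relative rules raise the bar in the severe stratum and so offset its advantage. The simulated power difference is about −0.5 to +1.8 points.

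**6. Fisher's test.** Its level is 2.6-3.3 % even when the stratum has no effect at all (odds ratio 1). In the model on the plan's inputs it is 2.4-3.1 %, and power is 7-9 points below chi-squared. Most of that is discreteness.

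**The case against.** The strongest reply is that nothing is invalid. The planned test errs on the conservative side, so it cannot manufacture a benefit. Unstratified tests of unpowered secondary proportions are ordinary practice, and under the plan's own inputs the loss is close to nil. All of this stands, and it fixes the point as minor.

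It may also be said that a stratified responder analysis is a detail for an analysis plan that is not shown. That would answer silence, but the article names a test and the named test omits the stratum. The ANCOVA does use the variable that defines the strata, but only for the primary change score.

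A reader might infer three stronger things that the document does not support:
- **That the test definitely runs well below 5 % and loses material power.** This needs a strongly prognostic stratum. The article gives neither stratum-specific response rates nor a baseline SD, and the entry range makes a correlation of 0.5 hard to reach.
- **That the main clinical-relevance outcome is affected.** No responder cut-off is designated as main. All three are secondary, and the 80 % power does not apply to them.
- **That Fisher's low level and power are the price of ignoring the strata.** They are mostly present when the stratum has no effect.

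**Conclusion.** The point holds as a minor matter of efficiency. Randomisation is stratified, the stated responder tests are not, and the effect, where there is one, is conservative. For the 1.5-point rule the chi-squared level is about 4.3-5 % with a power loss of about 0-1 point at a baseline-change correlation of about 0.15-0.3. At 0.5 the level is about 3.3-4 % and the loss about 2-4 points. The lower correlations fit the plan's inputs and the 4-10 entry range better, but the article cannot settle it. For the 30 % and 50 % rules the difference is within about 2 points in either direction. These figures rest on an assumed mean sham improvement of 1.0 and on assumed baseline distributions. The primary analysis and its sample size are not touched by this point.

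**What to change.** In Statistical analysis, state that the three PI-NRS responder outcomes will be compared by a Cochran-Mantel-Haenszel test stratified by the randomisation stratum (PI-NRS 4-6 versus 7-10), with the stratum-adjusted risk difference and its 95 % CI. Keep the unstratified table as descriptive.

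The cost is one sentence. The stratum is known for every randomised patient, the method is available in the SAS package already named, and no extra patients or data are needed. The change should be made before the data are unblinded.
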